*Data Management:* SPSS-PC software (version 18) will be used for data entry and analysis. The

Information will be exported from Microsoft Access to SPSS. Back-up data will be maintained on password protected USB drives. Each participant will be given a unique numeric code for all computer data records to maintain confidentiality. All data will be kept in locked offices and file cabinets and files will be protected with passwords.

*Pre-testing:* Prior to official recruitment, we will recruit a total of 15 households as pre-testers of the research process. The pre-testers will be asked to evaluate the interview questions, translation and understandability and content. The research protocol will be followed by the RAs and evaluated by them for use. The data collected will be evaluated for completeness and consistency. RAs will be evaluated for protocol accuracy. In the event that questions prove unclear or difficult to answer, the interview will be modified and retested.

*Missing Data:* Missing data are expected to be minimal based on our extensive pilot work. In the event

of household loss those households will be included in the analysis. Additionally, those households that drop out of the study will be compared to those who remained to determine any differences between the groups at baseline and at subsequent times for descriptive purposes and to determine if data is missing at random. Any variables that are related to the missingness will be included as covariates in the model and multiple imputations with chained estimation will be used to estimate missing data. We will conduct a residual analysis following the multilevel models to compare the residuals for models using completers only, all subjects without multiple imputation, and all subjects with multiple imputation to understand any biases introduced by missing not at random.

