*Data Analyses:* All analyses will be based on intent-to-treat principles. Multilevel modeling will be used to test Specific Aim 1 to determine the effectiveness of a village-led microfinance program on general health, psychological health (depression, PTSD, suicidality) and reintegration (stigma, reintegration/acceptance by family) in intervention villages compared women in control villages. Time (baseline, 6, 12, and 18 months) will form the first level of the model and women the second level of the model. Logistic or normal distribution models will be used depending on the scale of measurement for the outcome variable. Variables related to missingness will be included in the second level of the model along with group (intervention vs. control) as an independent variable predicting change over time. A significant coefficient for group would imply that the pattern of change in the outcome variable differed for the intervention and control households. Separate analyses will be conducted for the target woman and second member of each household. Similarly, multilevel modeling will also be used to test Specific Aim 2 to determine the effectiveness of a village-led microfinance program on household (food security, children in school, utilization of health care services) economic stability in intervention households compared to control households. In these analyses, household will be the second level of the model.

Overview of Specific Aim #3.

To achieve specific aim 3, village residents (n=5 in each intervention/control village, total n=50) will complete a baseline and 18-month post-baseline in-depth qualitative interview with the village-based RA and/or study coordinator. The interview will provide an in-depth examination of the role of economic stability on village-level health, stigma and reintegration in both intervention and control villages.

*Recruitment and Data Collection;* The research team will work closely with village based RA to identify 5 village female and male residents in each participating village who are eligible (16 years or older) and willing to participate in two 90 minute in-depth interviews. The interviews will be completed at baseline and 18-months post-baseline and will examine their perspective on the impact of household economic security on health, stigma, and reintegration of survivors of trauma and violence into their village. The participants will not have been previously interviewed.

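### The residual comparison planned to reveal bias from data missing not at random (MNAR) cannot do so, and the missing-data covariate rule is not limited to baseline variables

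*Protocol*

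**What the plan says.** Under Missing Data (protocol, Approach), dropouts are compared with stayers, with this stated aim: "determine any differences between the groups at baseline and at subsequent times for descriptive purposes and to determine if data is missing at random". The covariate rule follows: "Any variables that are related to the missingness will be included as covariates in the model". In addition, "multiple imputations with chained estimation will be used to estimate missing data". The section ends with a comparison of residuals from three multilevel fits (completers, all participants without imputation, all participants with imputation), whose stated purpose is "to understand any biases introduced by missing not at random". It expects little missing data but gives no rate.

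Data Analyses says where the covariates go: "Variables related to missingness will be included in the second level of the model along with group (intervention vs. control) as an independent variable". These person-level terms are meant to explain how the outcome changes across visits, and a significant group term is read as a difference between arms in that change. The group coefficient at that level is therefore the test of the intervention.

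**The concern.** Two steps are assigned jobs they cannot do, and a third is left too open.

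- **Residual comparison.** MNAR means that, given everything observed, the chance of being missing still depends on the unseen value. None of the three fits models this. The completers fit needs data missing completely at random (MCAR), or loss that depends only on modelled covariates. The other two assume MAR, since no departure from it is stated for the imputation.
- **Dropout comparison.** Observed differences between dropouts and stayers can argue against MCAR. They cannot separate MAR from MNAR, because that depends on values nobody has seen.
- **Covariate rule.** If a selected variable is measured after the loan and changed by it, conditioning on it alters what the group coefficient estimates.

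Agreement between the three fits could be read as evidence that MNAR bias is small when it is no such evidence. The open covariate rule also lets post-randomisation data help choose the adjustment set for the main test.

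**Working it through.** **Plan's own figure.** The Missing Data text contains no number to reproduce. The sample size paragraph gives power of .94/.89/.83 (physical score) and .91/.84/.78 (mental score) at ICC .001/.005/.010 with 300 per group. It omits the mean, SD and within-person correlation, so absolute power cannot be rebuilt. The standardised effect can be back-solved, assuming a two-sided test and 60 households per village (600/10):

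- Design effect at ICC .001: 1 + 59 × .001 = 1.059.
- Physical: d = (1.960 + 1.555) × √(2 × 1.059/300) = 3.515 × 0.0840 = 0.295.
- Mental: d = (1.960 + 1.341) × 0.0840 = 0.277.

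These values return .94/.888/.818 and .91/.847/.768, within about 2 points of the stated figures. Here 0.295 serves only as a rough yardstick.

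**Step 1: can the residual comparison respond to MNAR?** Assume 300 per arm and 26% missing (32% in the intervention arm). Subtract a shift delta from the unseen intervention outcomes and refit.

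| delta (SD) | Effect in full data | Completers: estimate, residual SD | Imputed: estimate, residual SD |
|---|---|---|---|
| 0 | 0.345 | 0.378, 0.784 | 0.379, 0.783 |
| 0.25 | 0.265 | 0.378, 0.784 | 0.379, 0.783 |
| 0.5 | 0.184 | 0.378, 0.784 | 0.379, 0.783 |
| 1.0 | 0.023 | 0.378, 0.784 | 0.379, 0.783 |

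The full-data effect nearly vanishes and nothing in the comparison moves. This holds by construction: delta changes only values that none of the fits can see.

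**Step 2: how large could the undetected bias be?** All inputs are assumptions: no true effect, baseline-to-final correlation 0.5, control losses random, intervention losses depending on the unseen final score at log-odds −1 per SD, 300 per arm, 5 imputations, 1,500 replicates (Monte Carlo error about 0.002). The final score is regressed on group and baseline.

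| Missing | Bias, completers | Bias, imputed | Residual SD, completers / imputed |
|---|---|---|---|
| 3% | 0.022 | 0.021 | 0.862 / 0.862 |
| 5% | 0.038 | 0.038 | 0.860 / 0.860 |
| 12% | 0.082 | 0.082 | 0.853 / 0.853 |
| 20% | 0.135 | 0.135 | 0.847 / 0.847 |

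Against 0.295 this is roughly 7% (0.022/0.295), 13%, 28% and 46%. The fit to everyone without imputation is not shown separately. With only the final score missing, it draws on essentially the same information as the completers fit.

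**Step 3: covariates.** Let tau be the total group effect on change, a the effect of group on the covariate, and b the effect of the covariate on change. If the covariate is allowed to predict change, the adjusted group effect is tau − a × b. With tau = 0.28 and assumed a and b:

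- a = .1, b = .3: 0.28 − 0.03 = 0.25
- a = .2, b = .3: 0.28 − 0.06 = 0.22
- a = .3, b = .5: 0.28 − 0.15 = 0.13
- a = −.2, b = .3: 0.28 + 0.06 = 0.34

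Simulation agrees (0.250, 0.222, 0.132, 0.336). A baseline covariate leaves the estimate at 0.28. A covariate entering the intercept only does not disturb the group-by-time effect.

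**The case against.** The strongest objection concerns the covariates. A reader might infer that the plan will adjust for 6- or 12-month variables and so remove part of the treatment effect. The protocol does not support that. The comparison at later visits has two stated purposes, description and judging MAR, and the covariate sentence stands apart from it. Placement at the person level beside group most naturally suggests fixed characteristics. Repeated scores of the same outcome are already responses at the first level, so they would not normally reappear as predictors. Distortion needs a selected variable that is post-baseline, changed by the loan and predictive of change, and it may go upward as well as downward. What stands is narrower. The rule covers any variable related to missingness, and person-level placement does not exclude a follow-up value, since that is also one number per person. The protocol itself expects the loan to change health and household economics at follow-up.

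On MNAR, it is fair to say that little missing data is expected, that the simulated mechanism is one choice among many, and that comparing the three fits usefully shows sensitivity to discarding incomplete cases. All of this stands. Low missingness shrinks the bias; it does not make the check informative about MNAR.

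Finally, a delta-adjusted analysis could properly be left to an SAP, so its absence is not the finding. The finding is that the protocol names a method for a purpose it cannot serve.

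**Conclusion.** The MNAR point holds in full and depends on no assumed number. Agreement between the three fits does not exclude MNAR, and disagreement would not demonstrate it. The dropout comparison can speak against MCAR but cannot establish MAR.

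The size is illustrative: about 0.02 SD at 3% missing to 0.13 SD at 20%, under the assumed mechanism. No single figure from that range should be quoted as the expected bias, because the protocol gives no rate and the 0.295 SD yardstick is back-solved.

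The covariate point is secondary and conditional. The text permits adjustment for variables the loan may have changed; it does not say this will happen, and neither the direction nor the size of any bias can be fixed from the protocol. The wording should be changed, but neither point shows that the trial's result will be biased.

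**What to change.** 1. Replace the residual comparison, as the MNAR check, with a delta-adjusted (pattern-mixture) analysis. Impute under MAR, shift the imputed values over a stated range separately in each arm, and report the shift at which the conclusion changes. The three fits may stay, described as sensitivity to incomplete cases and to imputation.
2. Delete the claim that comparing dropouts with stayers determines MAR. Keep the comparison as description.
3. Limit outcome-model covariates to baseline variables, preferably named in advance. Use post-baseline predictors of dropout only as auxiliary variables in the imputation model.

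The cost is analysis wording and a few more imputation runs. No new data are needed, and the stated power figures do not change.

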*Sample size calculation:*  We used data from Roberts and colleagues^56^ study of the reliability and validity of the SF-8 with a conflict-affected population in northern Uganda as the basis for our power analyses. We based the power analysis on repeated measures ANOVA, but propose to use multilevel modeling for the analyses that allows all cases with missing data to be included in the analyses. We do not have adequate estimates of the within and between variance to estimate power for the multilevel model directly. However, in general multilevel model approaches are more powerful than repeated measures ANOVA^62^. Since we do not have an estimate of the intraclass correlation (ICC) (individuals nested within villages) we varied the ICC from .001 to .010. For a sample size of 300 per group and assuming no change from baseline to 18 months in the control group and a 10% improvement in the intervention group, an alpha level of .05, the power to detect a significant group by time interaction for the physical health component score of the SF-8 Is .94, .89, and .83 for ICCs of .001, .005, and .010, respectively. Similarly power to detect a significant group by time interaction for the mental health component score of the SF-8 is .91, .84, and .78 for ICCs of .001, .005, and .010, respectively.

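### Nine named outcomes, six of them analysed in two household members, are each tested for effectiveness with no primary outcome, member or time point, so the chance of at least one false positive is about 20% to 58% rather than 5%

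*Protocol*

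**What the plan says.** All places are in the Protocol.

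- **Aim 1 outcomes** (Data Analyses): "general health, psychological health (depression, PTSD, suicidality) and reintegration (stigma, reintegration/acceptance by family". These are six constructs. The Sample size calculation treats the SF-8 as two component scores, so general health may mean two outcomes, making seven.
- **Aim 2 outcomes** (same paragraph): "household (food security, children in school, utilization of health care services) economic stability". These are three outcomes at household level: "In these analyses, household will be the second level of the model".
- **Members** (in the Aim 1 description): "Separate analyses will be conducted for the target woman and second member of each household".
- **Visits**: "Time (baseline, 6, 12, and 18 months) will form the first level of the model and women the second level of the model". They enter one longitudinal model per outcome.
- **Decision rule**: "A significant coefficient for group would imply that the pattern of change in the outcome variable differed for the intervention and control households". It gives no significance level and does not order the outcomes.
- **Level**: .05 appears only in the Sample size calculation, which takes "an alpha level of .05, the power to detect a significant group by time interaction for the physical health component score of the SF-8" and then does the same for the mental score. Neither score is called primary.

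The Specific Aims word the hypotheses at 6, 12 and 18 months without singling one out.

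**The concern.** The trial has a confirmatory purpose. The Specific Aims seek a science base for large-scale implementation, and the section on the importance of the knowledge gained aims at a causal conclusion. For such a trial the protocol should say which result decides it. This one has its own analysis section, and that section gives every outcome and both members equal standing.

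Two things follow. If the loan does nothing, the chance that at least one of the listed tests comes out significant is several times the nominal 5%, and the text does not stop that one result from being reported as evidence of effectiveness. Also, the two outcomes for which 300 households per group were judged sufficient carry no more weight than those for which no power was computed.

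**Working it through.** **1. The plan's own figures.** The protocol states no familywise error rate. Its stated power can be checked only for internal consistency, because the SF-8 means, SDs and within-person correlation are not given. Inputs: 300 per group in 10 villages, so m = 600/10 = 60 per village; two-sided .05 (sidedness assumed); design effect 1 + (m − 1) × ICC, which is 1.059, 1.295 and 1.590 at ICC .001, .005 and .010. Anchoring on the stated power at ICC .001:

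- Physical: 1.960 + z(.94) = 3.515. At ICC .005, Φ(3.515 × √(1.059/1.295) − 1.960) = .888; at .010, .818. Stated: .89 and .83.
- Mental: 1.960 + z(.91) = 3.301. This gives .847 and .768. Stated: .84 and .78.

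All lie within 2 percentage points, so the series is consistent with a one-degree-of-freedom test of each score at an unadjusted .05.

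**2. Number of tests.**

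- Named outcomes: 6 + 3 = 9, or 7 + 3 = 10 with the SF-8 split.
- With the second member, for Aim 1 only: 6 × 2 + 3 = 15, or 7 × 2 + 3 = 17.

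**3. Chance of at least one false positive.** All nulls are taken as true, with .05 two-sided per test.

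- Independent tests: 1 − .95^k.
- Equal correlation ρ between test statistics (assumed; the protocol gives none): 1 − ∫ [Φ((1.96 − √ρ x)/√(1 − ρ)) − Φ((−1.96 − √ρ x)/√(1 − ρ))]^k φ(x) dx.
- Only results favouring the loan, independent: 1 − .975^k.

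| k | Independent | ρ = .3 | ρ = .5 | ρ = .7 | Favouring the loan, independent |
|---|---|---|---|---|---|
| 9 | 37.0% | 32.6% | 26.9% | 20.2% | 20.4% |
| 10 | 40.1% | 35.1% | 28.7% | 21.3% | 22.4% |
| 15 | 53.7% | 45.7% | 36.1% | 25.6% | 31.6% |
| 17 | 58.2% | 49.3% | 38.6% | 27.1% | 35.0% |

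For one designated test the figures are 5%, and 2.5% in the favourable direction. At ρ = .3 to .7 the favourable-only figures fall to between 10.1% (k = 9, ρ = .7) and 25.4% (k = 17, ρ = .3).

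**4. Power under Holm with two SF-8 primaries.** At the first step the level is .05/2 = .025, with critical value 2.241. From each stated power p, the new power is Φ(1.960 + z(p) − 2.241).

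| Score | ICC | Stated | At .025 |
|---|---|---|---|
| Physical | .001 | .94 | .90 |
| Physical | .005 | .89 | .83 |
| Physical | .010 | .83 | .75 |
| Mental | .001 | .91 | .86 |
| Mental | .005 | .84 | .76 |
| Mental | .010 | .78 | .69 |

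**The case against.** **A statistical analysis plan may control multiplicity.** It may exist and is not shown, so the lack of an adjustment procedure is not itself a finding. That stands. But which outcome, member and time point decides the trial is a protocol choice, and this protocol sets an unranked rule in its own analysis section.

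**The inference is outcome by outcome.** The rule speaks only of the outcome variable tested, Aims 1 and 2 are separate hypotheses, and nowhere does the text say that any single significant result establishes effectiveness. That is also true, and pooling the aims is the reviewer's choice. Keeping them apart does not remove the problem. Aim 1 in the target woman alone gives 26.5% (6 tests) or 30.2% (7) under independence, and Aim 2 gives 1 − .95³ = 14.3%.

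**Stronger readings that the text does not support.** A reader might take the three follow-up visits as separate tests and count 10 × 2 × 3 = 60, with a 95.4% chance of a false positive. The analysis described is one longitudinal model per outcome with one group coefficient, and only the hypotheses are worded visit by visit. That count also doubles the Aim 2 outcomes, which are analysed once per household. A reader might also conclude that a false claim of effectiveness is more likely than not. Above, the any-direction figure passes one half only for 15 to 17 independent tests, while these outcomes are probably correlated, and no favourable-only figure for 9 to 17 tests exceeds 35%.

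**The .05 level is an inference.** It is stated for the SF-8 power calculation only. Applying it to the other outcomes is reasonable, but the protocol does not say so.

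**Conclusion.** The point holds in this form: nine named outcomes (ten with the SF-8 split), six or seven of them analysed in two members, are tested for effectiveness and none is designated to decide the trial. Followed as written, the chance of at least one false positive is about 4 to 12 times the nominal 5%. The lower end is nine strongly correlated tests; the upper end is 17 independent ones. In the direction that would support the loan, the excess over 2.5% is smaller in absolute terms but still severalfold.

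The size rests on three assumptions: .05 for every outcome, two-sided tests, and equal correlations of .3 to .7 chosen to span a plausible range. The missing designation rests on none of them. It should be corrected, but it does not invalidate the design.

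**What to change.** In Data Analyses, name the two SF-8 component scores in the target woman (the index participant) as the primary outcomes. Use the group by time test that the Sample size calculation powers, with Holm at an overall .05. Alternatively, name one SF-8 score as the single primary. State that the other Aim 1 outcomes, all Aim 2 outcomes and the second member's analyses are secondary, reported with confidence intervals and not used alone to claim effectiveness.

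One matter must be settled before the decisive time point is written in. Delayed Control Households has controls receiving their pig once the project's first year is over. Table 2 places that delivery in Year 3, third quarter, after six quarters of the intervention. The Sample size calculation assumes change to 18 months. These passages must be reconciled. If the decisive contrast became a single earlier visit, the stated power would not carry over to it.

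The change needs no new data. Its cost is the loss of power under step 4 of the working, which is largest at ICC .010, where the mental score falls from .78 to about .69. This is the worst case under Holm, since once one score is significant the other is tested at the full .05. Naming a single SF-8 primary avoids the loss.

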## Importance of knowledge gained and potential benefits of the proposed research to the participants and others

Trauma and violence is a global health issue and is a violation of human rights and has been used as a weapon of war in the DRC. The multiple interrelated and complex social determinants of health, such as poverty, stigma, chronic stress and trauma, and limited access to health care services impacts the health of individuals, their household and village. As a major donor to global health and humanitarian crisis, the US needs improved evidence of sustainable community-led intervention models for improved health outcomes to reduce health disparities in low-income countries. Research findings from the three study aims will inform the science base for large-scale implementation of structural interventions, with the aim to establish a causal relationship between a village-led microfinance intervention and increased health, household economic stability, and reintegration for survivors of trauma and violence. Further, the study will provide the basis for the transferability of the intervention to other settings, including man-made and natural disaster settings.

Table 2: Study Timeline

| **Activity** | **Year 1** | | | | **Year 2** | | | | **Year 3** | | | | **Year 4** | | | | **Year 5** | | | |
| --- | --- | --- | --- | --- | --- | --- | --- | --- | --- | --- | --- | --- | --- | --- | --- | --- | --- | --- | --- | --- |
|  | Q1 | Q2 | Q3 | Q4 | Q1 | Q2 | Q3 | Q4 | Q1 | Q2 | Q3 | Q4 | Q1 | Q2 | Q3 | Q4 | Q1 | Q2 | Q3 | Q4 |
| IRB approval/study set-up/training of RAs/village consent | X | X | X | X |  |  |  |  |  |  |  |  |  |  |  |  |  |  |  |  |
| Recruitment/retention (Household) |  |  |  | X | X |  |  |  |  |  |  |  |  |  |  |  |  |  |  |  |
| PFP Intervention households |  |  |  |  | X | X | X | X | X | X |  |  |  |  |  |  |  |  |  |  |
| Delayed control households (association meetings) |  |  |  |  | X | X | X | X | X | X |  |  |  |  |  |  |  |  |  |  |
| Delayed control households (intervention) |  |  |  |  |  |  |  |  |  |  | X |  |  |  |  |  |  |  |  |  |
| Follow-up contacts (intervention/control) |  |  |  |  |  | X | X | X | X | X | X | X | X | X | X | X |  |  |  |  |
| Retention follow-ups (intervention/control) |  |  |  |  |  | X | X | X | X | X | X | X | X | X | X | X |  |  |  |  |
| Fidelity Monitoring |  |  |  |  |  | X |  | X |  | X |  | X |  | X |  | X |  | X |  |  |
| Qualitative Interviews (intervention/control households) |  |  |  |  | X |  |  |  |  | X | X |  |  |  |  | X |  |  |  |  |
| DSMB meets |  | X |  | X |  | X |  | X |  | X |  | X |  | X |  | X |  | X |  | X |
| Data entry |  |  |  | X | X | X | X | X | X | X | X | X | X | X | X | X | X | X |  |  |
| Data Cleaning |  |  |  |  |  |  |  | X |  |  |  | X |  |  |  | X |  | X |  |  |
| Data Analysis |  |  |  |  |  |  |  |  |  |  |  | X | X | X | X | X | X | X | X | X |
| Annual Reports |  |  |  | X |  |  |  | X |  |  |  | X |  |  |  | X |  |  |  | X |
| Manuscripts & Dissemination |  |  |  | X |  |  |  | X |  |  |  | X |  |  |  | X |  |  | X | X |
|  |  |  |  |  |  |  |  |  |  |  |  |  |  |  |  |  |  |  |  |  |

Q1=Sept-Nov; Q2=Dec-Feb; Q3=March-May; Q4=June-August

